### 2.9. Primary Outcomes

#### 2.9.1. Fundamental Motor Skills (FMSs)

These will be assessed by means of the test of gross motor development-second edition (TGMD-2) [24]. This battery measures 12 FMSs in two different domains (locomotor skills and object control). The locomotor skills domain contains 6 assessments: (i) running, (ii) galloping, (iii) hopping on one foot, (iv) long jumping, (v) horizontal jumping and (vi) lateral sliding. The object control domain also includes 6 assessments: (i) batting a stationary ball, (ii) stationary dribbling, (iii) catching a ball, (iv) kicking a ball, (v) throwing a ball and (vi) rolling a ball. Estimated administration time is ≤10 min per child. The 6 locomotion skills and 6 object control skills incorporate 24 criteria, allowing a total score from 0 to 48 points. The domain scores can be transformed into a standard score (median = 10.0 and standard deviation = 3.0) and subsequently into a gross motor quotient (median = 100.0 and standard deviation = 15.0). This information can be found in percentiles that allow the child to be placed in normative values with respect to a reference population. The original TGMD-2 reports high test–retest and inter-rater reliability (all r values > 0.85), as well as good internal consistency that varies between 0.85 and 0.88 for each ability [24]. In addition, its content, construct and concurrent validity have been demonstrated in children aged ≥ 3 years in countries such as Chile [25,26], Brazil [27] and Korea [28]. 

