#### 2.9.2. Language Development

The language test for preschoolers (TELEPRE) [29] will be used. The purpose of this assessment is to measure the language of children in initial educational levels (3 to 6 years old) by means of 4 domains: (i) language comprehension, (ii) language expression, (iii) vocabulary and (iv) language description. The administration of the instrument requires a booklet of questions, various objects (bottle, toy car, pencil, plate, needle, cup, paintbrush, screw, sponge, small ball, button, small book, spoon, scissors, matchbox; plus three objects that serve as distractors) and 3 pictures representative of situations (i.e., serving milk to a cat, setting the table and being in a toy store) to be described by the child. To administer the instrument, a room free from noise or other distraction is required, in which the evaluator, the child and a classroom assistant will be present. The estimated application time is ≤25 min. The test scores vary according to the domain and age of the child being evaluated; they are described in detail below, according to the original manual [29]. To interpret the scores, the original manual [29] proposes the use of T-scores (average = 50 points and standard deviation = 10). Regarding the validation of the instrument, its internal consistency varies between 0.87 and 0.93, according to the domain analyzed and a concurrent validity with the test of psychomotor development (TEPSI) [29].

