#### 2.9.3. Physical Activity Level

This will be objectively monitored by accelerometers (ActiGraph GT9X, Pensacola, FL, USA). The device will be worn at the waist on an elastic belt, at the mid-axillary line on the right side. Children will be instructed to wear the accelerometer 24 h a day, for at least 7 days, including 2 weekend days, and only to remove the device when bathing or engaging in water activities [30]. The minimum amount of data considered acceptable for analysis purposes will be five days (including one weekend day) [30], with at least 10 h/day of wear time. LPA, MVPA and SB, following the cut-off points proposed by Lettink et al. [31], will be considered for analysis. Sleep time will not be taken into account. Data will be verified using Actilife software version 5.6 (ActiGraph, Pensacola, FL, USA). Consecutive 20 min blocks of 0 count will be considered as non-use of the device and discarded from the analyses. Data will be collected at a sampling rate of 30 Hz, downloaded in one-second periods, and aggregated over 15-s periods [32]. 

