### 2.12. Intention-to-Treat Analysis

A two-factor repeated measures ANOVA will be used to determine the effects of the intervention on the outcomes (group × time). Post hoc tests will be performed with an alpha adjusted by Bonferroni to identify statistically significant differences. The effect sizes will be calculated utilizing Cohen’s d [36] within the group and between the groups, using the following equation: effect size = (post-mean − pre-mean)/standard deviation combined. The level of significance will be set at 5%. The intraclass correlation coefficient will be used to verify the measurement’s reliability, with a predetermined threshold of 0.80 being used to include the data in the analyses. Furthermore, logistic regression will be performed to identify the association of the physical activity level with FMSs, language development and morphological and sociodemographic variable factors. For all statistical analyses, the sociodemographic variables will be considered as moderators (covariates). 

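### The supplementary association analysis fits logistic regression to continuous accelerometer time with no binary outcome defined and too many candidate predictors, and all sociodemographic items enter every analysis under an ambiguous label

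*Protocol article*

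**What the plan says.** Section 2.9.3 of the protocol article records physical activity with a waist-worn accelerometer. Data are "downloaded in one-second periods, and aggregated over 15-s periods", and the analysis variables are "LPA, MVPA and SB, following the cut-off points proposed by" a cited source. Such cut-offs sort epochs by intensity of movement. They do not sort children into active and inactive. What results for each child is an amount of time in each band, and the abstract and conclusions call the third one sedentary time.

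Section 2.12 has three relevant sentences:

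- The trial's test of the intervention: "A two-factor repeated measures ANOVA will be used to determine the effects of the intervention on the outcomes (group × time".
- An added association analysis: "logistic regression will be performed to identify the association of the physical activity level with FMSs, language development", and also with morphological and sociodemographic factors. No categorical version of physical activity is given in section 2.12 or elsewhere.
- A general rule: "For all statistical analyses, the sociodemographic variables will be considered as moderators (covariates".

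Section 2.13 carries the same procedures into the per-protocol analysis.

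The factors are described elsewhere. For motor skills (section 2.9.1), "This battery measures 12 FMSs in two different domains (locomotor skills and object control". Language (section 2.9.2) has "4 domains: (i) language comprehension, (ii) language expression, (iii) vocabulary and (iv) language description". Section 2.10.1 lists the morphological measures and section 2.10.2 a 12-item questionnaire.

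**The concern.** Logistic regression needs a categorical outcome. Choosing it for accelerometer time commits the trial to cutting a continuous variable, which loses information and makes the result depend on a cut that is not given. The list of factors is also long for 144 children. A logistic model with few events per predictor gives inflated coefficients, too many small p-values and an apparent fit that would not recur in new data. The reported correlates of activity in preschool children could then be artefacts.

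The general rule on sociodemographic variables raises a second issue. A moderator is examined through an interaction with treatment, whereas a covariate is adjusted for as a main effect. These are different models with different questions, and the sentence prescribes them for every analysis as if they were one.

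**Working it through.** The article states no sample size or power figure for the logistic regression, so there is none to reproduce. The calculation in section 2.3 sizes the locomotor comparison and is not used here.

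**1. Number of candidate predictors**

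- Motor skill domains (2.9.1): 2
- Language domains (2.9.2): 4
- Morphological measures (2.10.1): height, weight, BMI, waist and bicep circumference, four skinfolds = 9. BMI is computed from height and weight.
- Questionnaire items (2.10.2): 12, less the child's name = 11

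Total 2 + 4 + 9 + 11 = 26. With the 12 single skills in place of the two domains it is 36. With the single gross motor quotient it is 25. Coding multi-category items would add more.

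**2. Events per predictor (EPV)**

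EPV = N × min(p, 1 − p) / number of predictors. The proportion p is an assumption; p = 0.5 is the most favourable. The 15% loss in section 2.3 leaves 144 × 0.85 ≈ 122 children.

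| Model with 26 predictors | p = 0.5 | p = 0.3 | p = 0.2 |
|---|---|---|---|
| N = 144 | 72/26 = 2.8 | 43.2/26 = 1.7 | 28.8/26 = 1.1 |
| N = 122 | 61/26 = 2.3 | 36.6/26 = 1.4 | 24.4/26 = 0.9 |

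If each block is fitted separately with the 11 sociodemographic items (N = 144, p = 0.5):

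- Motor skills: 72/(2 + 11) = 5.5
- Language: 72/(4 + 11) = 4.8
- Morphological: 72/(9 + 11) = 3.6

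**3. Information kept after a split**

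For a normal variable the fraction kept is φ(z_p)² / [p(1 − p)].

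- Median split: 2/π = 0.637; 144 × 0.637 ≈ 92 children
- 30% split: 0.576; about 83 children
- 20% split: 0.490; about 71 children

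**4. Simulation** (1,000 runs per setting, N = 144, 26 independent normal predictors, no clustering)

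- One predictor truly correlated 0.25 with activity: power was 79% with linear regression and 67% with logistic regression after a median split. The mean logistic coefficient was 0.54 against a true 0.41, about 30% too large.
- No predictor related to activity, 50% split: mean apparent AUC was 0.75, and the overall likelihood-ratio test rejected in 12.5% of runs against a nominal 5%. On average 1.93 predictors had p < 0.05, against 26 × 0.05 = 1.3 expected. At least one did in 83% of runs, against 1 − 0.95^26 = 74% expected from 26 independent valid tests.

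The excess over the nominal rates is the overfitting. Sampling in classes of 12 would reduce the information further. I put no figure on this because the article gives no intraclass correlation.

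**5. What the moderator/covariate sentence does in the ANOVA**

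With two time points and complete data, the group × time test is a comparison of mean change. If each questionnaire item has one value per child (assumed), its main effect cancels in the change score and leaves that test as it was. Read as a moderator, each item instead adds a term that varies with group × time, so up to 11 such terms per outcome. The label therefore decides between no effect on the intervention test and a much larger model.

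**The case against.** The strongest reply is that this is a side analysis. The intervention is tested by the group × time ANOVA, physical activity is one of the outcomes tested there, and that test keeps it continuous. This stands. A reader might infer that the treatment effect on activity is to be dichotomised, and the document does not support that.

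Second, section 2.12 names four groups of factors and does not prescribe one model with 26 terms. This also stands: 2.8 is the best case on one reading. Fitting in blocks does not remove the problem, since the ratio stays at or below about 5.5.

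Third, the text speaks of an association and does not say outright that activity is the dependent variable. If the direction were reversed, motor and language scores would be the outcomes. These are scores too, again with no binary version defined, so the mismatch remains.

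Fourth, an article may leave the cut to a fuller document. The cut may be there, but the decision to use logistic regression is made here, and any cut costs information.

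Fifth, *covariates* in brackets may simply explain *moderators*, which points to main-effect adjustment. That is the more natural reading, and no interaction test is announced. A reader might count 11 items × 9 primary outcomes = 99 interaction tests, with about 5 false positives at 5%. The plan does not state such tests.

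Nor does it state that a child with a blank item is dropped. The ANOVA contains no class term, so covariates cannot be said to use up class-level degrees of freedom in it. Eleven main-effect covariates in 144 children (about 13 children each) is not clear overfitting.

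**Conclusion.** The concern holds for the association analysis. Its model does not fit the measured variable, and the factor list is too long for the number of children. At best about 64% of the information survives a split into two groups. This assumes a normal variable cut at the median, and less survives at other cuts. Events per predictor are at most 2.8 with all 26 variables and about 3.6 to 5.5 in blocks, before any loss of children. These figures rest on my count of the named variables and on an even split, neither of which the article fixes. The article also does not use minutes as the analysis unit; that the variables are times follows from how they are measured and named.

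The rule on sociodemographic variables is ambiguous in every analysis, including the intention-to-treat and per-protocol comparisons. No distortion of the intervention test is shown: harm there would require interaction terms or case deletion that the document does not specify. The point merits correction before analysis, but it does not undermine the main comparison.

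**What to change.** In section 2.12:

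- Replace the logistic regression with linear mixed regression of light activity, moderate-to-vigorous activity and sedentary time, each in minutes per day. Include wear time, since section 2.9.3 sets only a minimum, and a random intercept for class.
- Prespecify a short predictor list. One example is the two motor and four language domain scores, BMI without height and weight alongside it, and age. With wear time that is 6 + 1 + 1 + 1 = 9 terms, or 144/9 = 16 children per term.
- Replace the moderators (covariates) sentence with two. The first states that sociodemographic variables enter treatment comparisons only as a short, named list of covariates. The second states that any moderator analysis is a test of interaction with treatment and is exploratory.

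The change is to wording only, with no effect on data collection or sample size. The cost is that results come as differences in minutes rather than odds ratios, and fewer sociodemographic variables are adjusted for.

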### 2.13. Analysis by Protocol

For this analysis, only children who have completed more than 85% of the sessions will be included. The same procedures will be performed as those indicated for the intention-to-treat analysis.

## 3. Discussion

As mentioned in previous studies [11,12,13], FMS interventions lead to improvements in cognitive function, basic motor skills, language and memory in children aged 3 to 5 years. However, despite CMSI showing beneficial effects on basic motor skills and language in children [14,15], to date, there have been few studies that confirm its efficacy. This study responds to several concerns and needs identified in the specialized literature on motor competence, which suggests implementing interventions from early childhood, based on a robust methodology, in a structured learning environment and with a well-defined purpose [4,13]. 

The programs using CMSI for a period of 12 weeks, with one session per week, have demonstrated improvements in FMSs such as running, jumping, throwing, catching, stationary dribbling, rolling and kicking in South Asian children aged 5 to 6 years [15]. Similarly, Duncan, Cunningham and Eyre [14] found improvements in FMSs and language development following a 6-week intervention, consisting of one session per week, when using CMSI in England with children aged 3 to 5 years. 

This background supports the design to be implemented in the present protocol, which could show positive effects on FMSs in Chilean children aged 3 to 6 years. Since the effects of CMSI in Latin American children are unclear, this protocol will identify the effects on FMSs, language development and physical activity levels in Chilean children. Scientific evidence affirms that FMSs are an important precursor to psychological, social and physical benefits from the early stages of human development [5,37,38]. It is also recognized that language development is related to FMSs and motor competence from the early stages [7,8,9]. 

In this context and in order to avoid possible biases, children with musculoskeletal injuries, medical contraindications or congenital heart disease, and children with special educational needs such as visual, hearing, intellectual or multiple disabilities, dysphasia or autistic disorder that would impede their normal physical performance in the assessments and intervention, will be excluded. 

In addition, the study protocol has the strength to consider as secondary measures a series of morphological and sociodemographic variables in children aged 3 to 6 years. Morphological changes in preschoolers have been reported to lead to better reading comprehension [39]. In another study, conducted by Ferreira et al. [40], it was reported that children aged 6 to 7 years living in homes classified as adequate, located in neighborhoods outside the central region, and studying in private schools, had increased opportunities for better motor development in FMSs. 

All these variables and their respective indicators allow for the control of potential factors that go beyond the primary outcomes. Therefore, it is important to include these measurements in the programs for CMSI in children from 3 to 6 years of age, which can provide positive effects on these variables at an early age. If they do, then these interventions should be implemented in various schools with preschool classes. 

Further advantages of proposing such forms of intervention for Chilean children from 3 to 5 years of age in kindergartens and first grade are: (i) little space is required, and the intervention can be carried out in the classroom; (ii) little implementation is needed because most of the activities are carried out individually or in groups; (iii) low costs are required to carry out this type of intervention as a large number of these materials are already in the classroom; (iv) the variety of motor stories available can support high motivation and adherence to the intervention. 

Among the possible limitations of the study protocol are: (i) difficulty of recruiting children who can adhere to the study for the full 12 weeks plus the pre-intervention and post-intervention assessment periods; (ii) some children are unable to complete CMSI sessions due to illness or injury. 

## 4. Conclusions

This study protocol will analyze and compare the effects of CMSI on FMSs (locomotor skills and object control), language development (language comprehension, language expression, vocabulary and language description) and physical activity levels (light activity, moderate-to-vigorous intensity and sedentary time) in children aged 3 to 6 years. Our hypothesis indicates that CMSI has the potential to generate significant increases in locomotor skills, object control, language comprehension, language expression, vocabulary, language description and moderate-to-vigorous intensity of physical activity levels compared to control groups. If this intervention proves to be beneficial, it could contribute to the curriculum and comply with the indicative performance standards linked to establishments that provide education to children between 3 and 6 years of age. Moreover, this study represents a significant contribution to scientific knowledge in this line of research as, to the best of our knowledge, no studies using CMSI with Latin American preschoolers have yet been published. 

## Figures and Tables

**Figure 1 children-10-01530-f001:**
[figure not shown]
Study flowchart. Note: UMLEG: upper-middle-level experimental groups, UMLCG: upper-middle-level control groups, TL1EG: transition level 1 experimental groups, TL1CG: transition level 1 control groups, TL2EG: transition level 2 experimental groups, TL2CG: transition level 2 control groups.

**Figure 2 children-10-01530-f002:**
[figure not shown]
Assessments and usual sessions of the intervention. Legends: CMSI: combined movement and storytelling intervention. FMSs: fundamental motor skills.

**Table 1 children-10-01530-t001:** Summary of combined movement and storytelling intervention.

Motor Story	Materials	Warm-Up (5 min)	Main Part (25 min)	Cool Down (10 min)
Week 1: Who I am	Chairs, hoops, balls, mats, pencils, erasers and masking tape	Joint mobility exercises ^1^ and introduction to motor story	Locomotion skills ^2^ and verbal interaction ^4^	Return to calm ^5^ and feedback from the motor story
Week 2: We go on an excursion	Mats, chairs and rope		Notion and body image, and dynamic balance	
Week 3: The school	Mats, chairs, hula hoops and voice		Notion and body image, dynamic balance and visuomotor coordination	
Week 4: The recess	Mats, materials available in the patio or classroom		Dynamic balance, object control ^3^ and free play	
Week 5: The weekend has arrived	Music, blanket, mats, hoops, balls and newsprint		Object control ^3^ and verbal interaction ^4^	
Week 6: Visiting the park	Games found in the kindergarten playground and hula hoops		Dynamic balance, tone control, eye–motor coordination and object control ^3^	
Week 7: My days in the field	Lentil cones, and ping pong balls from reused paper		Dynamic balance, eye–motor coordination and free play	
Week 8: My days at the beach	Relaxing music, speaker and elements in hand		Sensorimotor, dynamic balance and visuomotor coordination	
Week 9: We go to the stadium	Exercise machines, speaker, relaxing music and relaxation audio		Dynamic balance, eye–motor coordination and free play	
Week 10: We are going to know my environment	Ball, relaxing music, speaker and voice		Dynamic balance and eye–motor coordination	
Week 11: Let’s go to the circus	Balls, ropes, mats and bottles		Locomotion skills ^2^, object control ^3^ and verbal interaction ^4^	
Week 12: Tell me your adventures	Speaker, relaxation music, sock balls and other materials available		Dynamic balance, eye–motor coordination and tone control	

Retrieved from Conde [22] and adapted by authors. ^1^ Included joint movements of the lower and upper limbs. ^2^ Included running, jumping, galloping, rolling and crawling, among others. ^3^ Included throwing, catching and kicking, among others. ^4^ For example, the teacher asks what animals live in the jungle and the children answer orally and then imitate some of them, through body movements. ^5^ Breathing exercises and stretching of the muscles involved in the activities.

## Data Availability

Not applicable.
